## Assignment of interventions: blinding

### Who will be blinded {17a}

This is a double-blind study. Patients and all clinical team members involved in the study are blinded. Solnatide and saline solution have the same appearance. All personnel except pharmacy staff directly involved in the study, including the investigator, are blinded to the medication codes.

Pharmacy staff in charge of labelling and preparing the IMP will be unblinded. As soon as a patient is randomized, an email will automatically be sent to the pharmacist instructing him or her to prepare a solnatide or saline (placebo) solution for that randomization number. The syringe containing 5 ml of either one or the other solution will be appropriately labelled and delivered to the ICU for administration. The pharmacist will then print and sign the email for filing purposes. No clinical staff member has access to the treatment preparation instructions except for the study pharmacists. The trial statistician will be blinded during the analysis of the data.

### Procedure for unblinding if needed {17b}

Individual patient unblinding during the trial may occur in case of patient emergencies or medically important adverse events including cases of COVID-19.

The code breaking procedure is managed by means of an online-specific utility implemented in the eCRF and is available for the investigator and pharmacovigilance staff only. Sealed envelopes will also be provided as backup in the unlikely case of system unavailability.

If during the study the investigator needs to break a code (for emergency reasons), he/she has to follow the procedure implemented in the system clicking on ad hoc icon present on the toolbar.

In case of an individual patient unblinding, an automatic email will be sent to the study team notifying the occurrence of a code break reminding the investigator to discontinue the patient from the study.

## Data collection and management

### Plans for assessment and collection of outcomes {18a}

All data collected for this trial, e.g., eligibility criteria, demography, medical history, concomitant medication, physical examinations, vital sign measurements, laboratory results, and ECG data, is first recorded in site specific clinical charts based either on electronic or paper documents. If electronic charts are used, the electronic system should be compliant with applicable requirements. No study-related information will be stored on the eCRF only.

For laboratory tests, each site uses its own certified routine laboratory, which also provides its own reference values for each parameter obtained for study purposes. Measurements like ECG or hemodynamic parameters will be obtained using medical-grade, certified equipment.

Clinical scores are assessed based on the following resources:
Gas exchange, Organ failure, Cause, Associated disease (GOCA) score [26, 27]Sequential Organ Failure Assessment (SOFA) [28]Acute Physiology and Chronic Health Evaluation (APACHE) II score [29]Simplified Acute Physiology Score (SAPS) 3 [30, 31]

### Plans to promote participant retention and complete follow-up {18b}

Not applicable as this is a study of patients with ARDS in intensive care and under mechanical ventilation.

### Data management {19}

Designated investigator staff will enter the data required by the protocol into the eCRF using fully validated software that conforms to 21 CFR Part 11 requirements as well as GAMP 5 and PIC/S requirements. Designated investigator site staff will not be given access to the Electronic Data Capture (EDC) system until they are trained.

Web-based software will be used and no installation procedure is needed. Each site will be authorized by the administrator to access the eCRF. Each site-qualified personnel will be allowed to access the eCRF by means of a “login mask” requiring user ID and password and may read, modify, and update only the information he/she previously reported. Each page reports site code and subject code.

Online validation programs will check for data discrepancies and, by generating appropriate error messages, allow the data to be confirmed or corrected before transfer to the CRO working on behalf of the sponsor. The investigator will certify that the data entered into the eCRF is complete and accurate.

After database lock, the investigator will receive a CD-ROM of subject data for archiving at the investigational site.

### Confidentiality {27}

Participant confidentiality and privacy is strictly held in trust by the participating investigators, their staff, and the sponsor(s) and their interventions. This confidentiality is extended to cover testing of biological samples and genetic tests in addition to the clinical information relating to participants. Therefore, the study protocol, documentation, data, and all other information generated will be held in strict confidence. No information concerning the study or the data will be released to any unauthorized third party without prior written approval of the sponsor.

All research activities will be conducted in as private a setting as possible.

The study monitor, other authorized representatives of the sponsor, representatives of the IRB/IEC, regulatory agencies, or pharmaceutical company supplying study product may inspect all documents and records required to be maintained by the investigator, including but not limited to medical records (office, clinic, or hospital) and pharmacy records for the participants in this study. The clinical study site will permit access to such records.

The study participant’s contact information will be securely stored at each clinical site for internal use during the study. At the end of the study, all records will continue to be kept in a secure location for as long a period as dictated by the reviewing IRB/IEC, institutional policies, or sponsor requirements.

Study participant research data, which is for purposes of statistical analysis and scientific reporting, will be collected and stored at the OPIS Data Center. This will not include the participant’s contact or identifying information. Rather, individual participants and their research data will be identified by a unique study identification number. The study data entry and study management systems used by clinical sites and by OPIS Data Center staff will be secured and password protected.

### Plans for collection, laboratory evaluation, and storage of biological specimens for genetic or molecular analysis in this trial/future use {33}

These are not applicable

## Statistical methods

### Statistical methods for primary and secondary outcomes {20a}

Data collected in this study will be listed and summarized as described below by treatment group. Data from all sites will be pooled and summarized. Continuous data will be summarized by mean, standard deviation (SD), median, first and third quartiles, minimum, and maximum. Categorical data will be presented by absolute and relative frequencies (n and %) or contingency tables. All statistical tables, listings, figures, and analyses will be performed by means of SAS® release 9.4 or later (SAS Institute, Inc., Cary, NC, USA).

A two-sided alpha level 0.05 will be considered. No alpha level adjustment will be made for secondary preliminary efficacy outcome variables and for multiple comparisons. Patients will be included in each analysis based on available assessments. No methodology for missing data handling will be applied, except for the EVLWI efficacy endpoint. Censoring rules for time-to-event analyses will be detailed in the Statistical Analysis Plan.

There is no primary efficacy endpoint as the primary objective of the study is to investigate the safety of solnatide. All efficacy analysis will be considered as secondary preliminary efficacy analyses. All secondary preliminary efficacy analyses will be performed based on the ITT set as primary analysis and on the PP set as supportive analysis and will be reported by planned treatment cohort.

No methodology for missing data handling will be applied for secondary preliminary efficacy endpoints, except for EVLWI. The homogeneity of treatment effects across different centers will not be tested.

#### Change from baseline to day 7 in extravascular lung water index (EVLWI)

The absolute change from baseline in extravascular lung water index (EVLWI) after 7 days from randomization, as assessed with a validated bedside measurement (single indicator transpulmonary thermodilution measurement, such as with PiCCO® from Pulsion or VolumeView from Edwards), will be analyzed by means of an analysis of covariance (ANCOVA) model with baseline value as covariate and treatment cohort as an independent class variable. Mean estimates will be provided, together with their corresponding two-sided 95% confidence intervals.

A hierarchical testing procedure will be carried out to control multiplicity, where statistical comparison will first be performed between the highest solnatide dose cohort and the placebo cohort. Statistical comparison between the next lower dose(s) and placebo will be performed only in case of statistical significance of the comparison between the highest solnatide dose cohort and the placebo cohort.

The analysis described above will be performed on data where the Last Observation Carry Forward approach is applied for handling missing data. Additional imputation methodologies for missing data may be applied as sensitivity analysis (further details to be provided in the Statistical Analysis Plan).
Secondary preliminary efficacy endpoints

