## Trial design {8}

This is a Phase IIb, randomized, placebo-controlled, double-blind, dose escalation study. The study will be conducted in up to 10 centers located in Germany and Austria. Additional European countries may be involved.

Thirty eligible patients with pulmonary permeability edema (EVLWI ≥ 10 ml/kg PBW) and moderate to severe ARDS admitted to an intensive care unit (ICU) and under mechanical ventilation will be randomized in a 2:1 ratio to receive either a low dose of solnatide (5 mg) (20 patients) or placebo (10 patients). Patients will be treated for up to 7 days and the study duration for each patient is of up to 28 days.

Following the end of the study period for these patients and prior to escalating from the low dose to the middle dose (60 mg), safety data collected during the 28-day study period will be reviewed by an independent Data Safety Monitoring Board (DSMB), who will decide whether the safety profile is acceptable for dose escalation. In case of positive outcome, 25 new patients will be randomized to solnatide 60 mg or placebo in a 4:1 ratio in order to have 20 patients randomized to the middle-dose group and 5 to the placebo group.

After the end of the study period of these patients and prior to escalating from the middle dose to the high dose (125 mg), safety data will again be reviewed by the DSMB, who will decide whether the safety profile is acceptable for escalating to the high dose.

If so, 40 new patients will be randomized to solnatide 125 mg and placebo in a 1:1 ratio in order to have 20 patients randomized to the high-dose group and 20 patients to the placebo group.

The randomization ratios solnatide/placebo (i.e. 2:1; 4:1; 1:1) will allow to have a total of 35 patients assigned to placebo. In addition, the randomisation schedule will provide the DSMB with enough placebo patients to perform the safety analysis.

To conduct the study, approximately 95 patients will therefore be randomized (see Fig. 1).

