#### Spontaneous Breathing Trial

The time (in days) from the first spontaneous breathing trial to the first successful extubation / unassisted breathing will be calculated. Summary descriptive statistics will be provided.

In addition, patients will be classified according to the following outcome definitions [32]:
SimpleSuccessful SBT after the first attemptDifficultFailed SBT at first attempt andRequired up to three trials orRequired < 7 days to reach successful SBTProlongedRequired > 7 days to reach successful SBT

#### Time to extubation through day 28

Time to extubation (in days) is defined as the difference between the first extubation date and the randomization date. Patients still intubated at day 28 or who die while still intubated will be censored at day 28. Summary descriptive statistics will be provided for the time to extubation.

#### Ventilator-free days (VFD) through day 28

VFD is defined as the number of days from randomization to day 28 after achieving unassisted breathing for patients who maintained unassisted breathing for at least two consecutive calendar days. If a patient survived for more than 48 consecutive hours of unassisted breathing but required assisted breathing (for any reason) before day 28, the number of VFD is the number of days of successful unassisted breathing through day 28. All periods of successful unassisted breathing (> 48 consecutive hours) are taken into account. Unassisted breathing is defined as being extubated with face mask, with nasal prong oxygen or room air or T-tube breathing or tracheostomy mask breathing or CPAP breathing with ≤ 8 cm H_2_O pressure support of assisted ventilator support, according to weaning protocol. Patients who die before day 28 will be assigned the number of days of successful unassisted breathing. If a patient required more than 28 days of mechanical ventilation, the value for VFD will be set to 0.

The parameter of ventilator-free days will be analyzed by means of an analysis of variance (ANOVA) model with treatment cohort as an independent class variable. Mean estimates will be provided, together with their corresponding two-sided 95% confidence intervals.

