## Trial status

Current protocol version: 8.0, 2 August 2021

Start of recruitment: 23.05.2018

Approx. date of completion: start + 4 years

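### The EVLWI and ventilator-free-day models compare each dose with one placebo cohort collected over three sequential randomized steps and have no step term, so part of any between-step difference would enter the dose effect.

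*Protocol article*

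**What the plan says.** **Design.** Trial design {8} describes three steps. Each opens only after the previous step's patients have finished their study period and the DSMB has agreed to escalate. Step 1 allocates "either a low dose of solnatide (5 mg) (20 patients) or placebo (10 patients"). Step 2 is sized for "20 patients randomized to the middle-dose group and 5 to the placebo group". Step 3 is 1:1, 20 and 20. The ratios "will allow to have a total of 35 patients assigned to placebo". The allocation section {16a-c} provides a separate randomization list for each step and no stratification factors, but gives the third ratio as 4:1, not 1:1.

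**Analysis.** EVLWI change to day 7 is analysed by ANCOVA "with baseline value as covariate and treatment cohort as an independent class variable". For the hierarchy, "statistical comparison will first be performed between the highest solnatide dose cohort and the placebo cohort"; lower doses are tested only if that comparison is significant. Ventilator-free days use an "analysis of variance (ANOVA) model with treatment cohort as an independent class variable", with the same gate and no covariate. No step, period or calendar-time term appears in either model. The article leaves censoring rules, further imputation methods and subgroups to the SAP, but states these model terms itself.

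**Timing.** Recruitment began on 23 May 2018. Trial status gives "Approx. date of completion: start + 4 years".

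**The concern.** Randomization makes a dose group comparable with the placebo patients drawn from the same list, that is, in the same step. It gives no such protection against placebo patients from the other two steps. A single cohort variable with one placebo level merges all 35, so each dose is set partly against patients recruited at another time. The word pooled is not used for placebo, but no other reading fits one class variable, one placebo cohort and a planned total of 35.

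If case mix or background care moved between steps, part of that movement would be reported as a dose effect. Some movement is possible over about four years: concomitant care is at the investigator's discretion, and sites or countries may be added. COVID-19 arose during the trial, since the unblinding section lists "medically important adverse events including cases of COVID-19". The baseline covariate absorbs only drift that acts through baseline EVLWI, and the ventilator-free-day model has no covariate at all. At stake is the review of candidate Phase III endpoints, which is the stated secondary objective.

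**Working it through.** **Inputs.** Placebo 10/5/20 and 20 per dose (Trial design {8}; Sample size {14}). Difference 3.2 ml/kg, SD 3.5, two-sided 0.05 (Sample size {14}). The size of any drift is an assumption, because the documents give none.

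**1. The plan's own power.** Two-group t-test, 20 vs 20, difference 3.2, SD 3.5: power 0.804. The stated 80% reproduces.

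**2. Non-concurrent share** = 1 - (placebo in the dose's own step / total placebo).

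| Dose | Step 3 at 1:1 (10/5/20) | Step 3 at 4:1 (10/5/5) |
|---|---|---|
| 5 mg | 25/35 = 71% | 10/20 = 50% |
| 60 mg | 30/35 = 86% | 15/20 = 75% |
| 125 mg | 15/35 = 43% | 15/20 = 75% |

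**3. Bias without a step term** = (outcome level in the dose's step) - (placebo-weighted mean level over the steps). For a jump of 1 ml/kg before step 3, the placebo mean moves by 20/35 = 0.57:
- 5 mg and 60 mg: 0 - 0.57 = -0.57
- 125 mg: 1 - 0.57 = +0.43

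Other patterns give other shares. A linear drift totalling 1 ml/kg (levels 0, 0.5, 1) moves the placebo mean by (5 x 0.5 + 20 x 1)/35 = 0.64, so the biases are -0.64, -0.14 and +0.36. A jump before step 2 moves it by 25/35 = 0.71, giving -0.71, +0.29 and +0.29. A drift in the opposite direction reverses all signs.

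**4. Type I error of the 125 mg test.** The pooled standard error is 3.5 x sqrt(1/20 + 1/35) = 0.98. The standardized bias is 0.43/0.98 = 0.44 for a 1 ml/kg jump and 0.86/0.98 = 0.87 for 2 ml/kg. Simulation (no drug effect, baseline covariate left out) gives about 7% and 13-14%. With step in the model it is about 5% in every pattern tried.

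**5. Type I error for 5 and 60 mg.** Tested without the gate, about 9% each at 1 ml/kg and 20% each at 2 ml/kg. With the gate and no active dose, about 0.5% and 1%. The jump pushes 125 mg and the lower doses in opposite directions, so few simulated trials reject both.

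**6. Cost of a step term.** Each dose occurs in one step only, so the term contrasts it with that step's placebo. SE = 3.5 x sqrt(1/20 + 1/n), where n is the placebo number used; power is for 3.2 ml/kg.

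| Comparison | n | SE | Power |
|---|---|---|---|
| Any dose, pooled | 35 | 0.98 | 90% |
| 125 mg, step term | 20 | 1.11 | 82% |
| 5 mg, step term | 10 | 1.36 | 65% |
| 60 mg, step term | 5 | 1.75 | 44% |

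If step 3 is 4:1, the 125 mg comparison also has 5 concurrent controls and about 44% power.

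**The case against.** **The drift is hypothetical.** This stands. No step dates are given, and the unblinding section does not say when, or in which step, COVID-19 patients entered. A reader might infer from the four-year span that the steps did differ; the documents do not show that. A 2 ml/kg jump is 2/3.2 = 63% of the design difference and should be read as a scenario only.

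**Not all drift becomes a dose effect.** This stands. In the patterns above, 0.14 to 0.71 of it enters, with a sign that depends on the dose, and baseline EVLWI may absorb some.

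**The gate protects the lower doses.** This stands when no dose works: the ungated 20% must not be quoted as their error rate under the plan. It does not protect their estimates and confidence intervals, and it no longer blocks the lower-dose tests once 125 mg is significant.

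**Pooling buys precision.** This stands in part. With root mean squared error = sqrt(SE² + bias²), a 1 ml/kg jump gives 1.14 pooled against 1.36 with step (5 mg), 1.14 against 1.75 (60 mg) and 1.07 against 1.11 (125 mg). Pooling wins for all three. At 2 ml/kg it gives 1.51, 1.51 and 1.30, so the step term wins for 5 and 125 mg but not for 60 mg. Accuracy on average does not, however, restore the 5% level of the gatekeeping test.

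**Safety.** A reader might extend the point to the safety tables. Those are descriptive, reporting by actual treatment cohort does not itself fix how placebo is laid out, and DSMB review follows each dose group, which has its own randomized placebo. The documents do not support calling this a defect.

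**Conclusion.** The point holds at should-fix level. The two models, as written, leave between-step differences in the dose comparisons, and the first hierarchical test is exposed: about 7% or 13-14% type I error under an assumed 1 or 2 ml/kg jump before step 3, with SD 3.5 and placebo 10/5/20. Without drift it stays at 5%.

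The shares of 43%, 71% and 86%, and the statement that 125 mg keeps its power, depend on a 1:1 third step. Under the 4:1 ratio in the allocation section the shares are 50-75% and that power is lost. The missing step term is a defect under either ratio.

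A must-fix reading might seem to follow, but there is no primary efficacy endpoint, the sample size rests on feasibility, and all efficacy analyses are secondary and preliminary.

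**What to change.** 1. Add randomization step (three levels) as a fixed factor to the EVLWI ANCOVA and the ventilator-free-day model, at least for the 125 mg test that opens the hierarchy. Each dose is then contrasted with its concurrent placebo, and the residual variance is still estimated from all patients.
2. Report the pooled-placebo model as a labelled sensitivity analysis. For 60 mg, with only five concurrent controls, present and read both models together.
3. Reconcile the third-step ratio between Trial design {8} with Sample size {14} and the allocation section, then restate the number of concurrent placebo patients and the power.
4. Optionally, show placebo by step beside the combined column in the safety tables. This is a matter of presentation.

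**Cost.** Only wording changes; no further patients or data are needed. Intervals widen: SE rises from 0.98 to 1.11 (125 mg), 1.36 (5 mg) and 1.75 (60 mg). The stated 80% for 20 vs 20 is kept for 125 mg if step 3 is 1:1; power for 5 and 60 mg falls from about 90% pooled to about 65% and 44%.

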### Sample size {14}

Given that the primary objective of the study is to investigate the safety of solnatide, the study sample size of 95 randomized patients is based on feasibility criteria.

Patients will be randomized to 3 groups of 20 patients each, representing the 3 multiple ascending dose groups receiving solnatide at doses of 5 mg, 60 mg and 125 mg, and 35 patients will receiving placebo in total, with 15 patients receiving placebo in Dosing Group A (low dose) and Dosing Group B (middle dose) and 20 patients receiving placebo in Dosing Group C (high dose).

Nevertheless, considering the key preliminary efficacy endpoint and the results of a Phase IIa study (2012-001863-64), a sample size of 20 evaluable patients in each treatment group will have approximately 80% power to detect a difference in means between solnatide and placebo of 3.2 ml/kg in the change from baseline to day 7 of EVLWI with a common SD of 3.5 using a two-group *t*-test with a 0.05 two-sided significance level and no alpha level adjustment for multiple testing.

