No multiplicity adjustment for multiple comparison will be applied, given that statistical comparison will be performed only between the highest solnatide dose cohort and the placebo cohort. A statistical comparison between lower dose(s) and placebo will be performed only in case of statistical significance of the comparison between the highest solnatide dose cohort and the placebo cohort.

#### Days of hospitalization through day 28

Length of hospital stay (in days) is defined as the difference between the discharge date and the randomization date. Patients still in the hospital at day 28 or who die during hospitalization will be censored at day 28. Days of outpatient hospitalization will not be included. Summary descriptive statistics will be provided for the number of days of hospitalization.

#### Days of stay at ICU through day 28

Length of stay at ICU (in days) is defined as the number of calendar days a patient was in the ICU. Patients still in the ICU at day 28 or who die during the stay at ICU will be censored at day 28. Summary descriptive statistics will be provided for the number of days of stay at the ICU.
2.Safety analyses

Safety analyses will be conducted on the Safety Set and will be reported by actual treatment cohort. No methodology for missing data handling will be applied for safety parameters.

#### Drug-related adverse events through day 14

The incidence of treatment-emergent drug-related AEs through day 14 after randomization, both in terms of number of events and in terms of patients with at least one event, will be tabulated by MedDRA System Organ Class (SOC) and Preferred Term (PT).

#### All adverse events through day 28

According to the onset date of the event, AEs will be defined as follows:
Treatment-emergent AEs are those events with an onset date after treatment initiation;Non-treatment-emergent AEs are those events with an onset date between screening and treatment initiation.

Non-treatment-emergent adverse events will be listed only. The incidence of treatment-emergent adverse events (TEAE) will be tabulated by MedDRA System Organ Class (SOC) and Preferred Term (PT). The incidence of TEAEs will also be summarized by system organ class, preferred term, and severity (based on investigator’s judgment).

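### The EVLWI hierarchy is said to control multiplicity, but it gates both lower doses on the highest dose alone, so the familywise error can reach about 9.4%

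*Protocol article*

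**What the plan says.** The section on change from baseline to day 7 in EVLWI specifies an ANCOVA with the baseline value as covariate and treatment cohort as class variable. It gives the testing order a purpose: "A hierarchical testing procedure will be carried out to control multiplicity". The highest dose is compared with placebo first. The condition for the rest is: "Statistical comparison between the next lower dose(s) and placebo will be performed only in case of statistical significance of the comparison between the highest" dose cohort and the placebo cohort. No further condition is placed between 60 mg and 5 mg.

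The general statistical methods section (20a) sets the level, "A two-sided alpha level 0.05 will be considered", and adds: "No alpha level adjustment will be made for secondary preliminary efficacy outcome variables and for multiple comparisons".

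The section on ventilator-free days (VFD) through day 28 uses the same gate, again with placebo as the comparator: "A statistical comparison between lower dose(s) and placebo will be performed only in case of statistical significance of the comparison between the highest solnatide dose". There the protocol claims no control. It says that no multiplicity adjustment is applied, and gives as the reason that only the highest dose is compared with placebo.

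On group sizes, the sample size section says "Patients will be randomized to 3 groups of 20 patients each, representing the 3 multiple ascending dose groups", and the trial design section says that the randomisation ratios "will allow to have a total of 35 patients assigned to placebo".

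**The concern.** A hierarchical procedure with every test at full alpha controls the familywise error in the strong sense only if each test is conditional on all the tests before it. Here the second and third tests are conditional on the first but not on each other. When the highest dose works, the gate opens and two further tests run side by side at 5% each. If neither lower dose works, there are two chances of a false positive, and the property claimed for the procedure is lost.

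At stake is the accuracy of that claim, and whether 60 mg or 5 mg is reported as significantly better than placebo on EVLWI, which the sample size section treats as the key preliminary efficacy endpoint.

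The VFD section has a related fault of reasoning. It justifies the lack of adjustment by saying that only one comparison is made, and its next sentence allows more.

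**Working it through.** **Inputs**
- Two-sided alpha 0.05 per comparison, no adjustment (section 20a and sample size section).
- 20 patients on each of three doses (sample size section); 35 placebo patients in total (trial design).
- Planned effect: a "difference in means between solnatide and placebo of 3.2 ml/kg in the change from baseline to day 7 of EVLWI", with SD 3.5 (sample size section).
- The lower doses are gated only on the highest dose (EVLWI section).

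**The plan's own figure.** For 20 against 20, the noncentrality is 3.2 / (3.5 × √(1/20 + 1/20)) = 2.89 on 38 degrees of freedom. The noncentral t gives a power of 80.4%, which agrees with the stated value of about 80%. Against 35 placebo patients the same effect has about 89% power in a two-group t-test.

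**Which configurations are exposed**
- *125 mg null.* Any false positive requires the 125 mg test to be significant, so the error is at most 5%.
- *125 mg effective, at most one lower dose null.* At most one true null lies behind the gate, so the error is at most 5%.
- *125 mg effective, both lower doses null.* Two true nulls are tested in parallel once the gate opens. Only this case can exceed 5%.

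**Maximum in the exposed case.** Let the gate be certain to open. The two lower-dose statistics share the placebo group, so their correlation is

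ρ = (1/35) / (1/20 + 1/35) = 0.0286 / 0.0786 = 0.364.

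The familywise error is 1 − P(|Z₁| ≤ 1.96 and |Z₂| ≤ 1.96) for a bivariate normal with this ρ, which gives **9.4%**. If the two tests were independent it would be 1 − 0.95² = 9.75%.

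**By true 125 mg effect.** These come from 1,000,000 simulated trials per row, with pooled-variance t-tests, 35 shared placebo patients, SD 3.5 and both lower doses null:

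| True 125 mg effect (ml/kg) | Gate opens | Error, rule as written | Error, strict 125 → 60 → 5 |
|---|---|---|---|
| 0 (global null) | 5.0% | 5.0% | 5.0% |
| 1.6 | 36.4% | 3.9% | 2.1% |
| 3.2 (planned) | 89.8% | 7.9% | 4.2% |
| 5 | 99.9% | 9.3% | 5.0% |
| 8 | 100% | 9.4% | 5.0% |

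With both 125 mg and 60 mg clearly effective and only 5 mg null, the rule as written gives 5.0%.

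**Sensitivity to placebo size.** The allocation section lists 4:1 for the third step where the trial design section gives 1:1. At 4:1 the placebo total would be 10 + 5 + 5 = 20. Then ρ = 0.5, the maximum is 9.1%, and the error at the planned effect is 6.4%. The conclusion does not change.

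**The case against.** The strongest reply is that a step-down was meant. The procedure is called hierarchical, the highest dose comes first, and the wording about the next lower dose has an order to it. The optional plural may only allow for an escalation that stops early. If escalation ends at 60 mg, only 5 mg lies below the highest dose and the rule is an ordinary fixed sequence that holds 5%. This is a fair reading of the intent, but the written condition names the highest dose and nothing else, and the VFD section repeats it in the same form. The EVLWI section defers only additional imputation methods to the SAP, not the testing rule.

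Four stronger readings are tempting, and the protocol does not support them:
- *That the familywise error simply is about 9%.* That figure is a maximum in one configuration, as the table shows.
- *That the statement of no alpha adjustment in section 20a proves the defect.* A valid fixed sequence also tests every step at the full 0.05, so the statement is compatible with control.
- *That the VFD section also makes a false claim of control.* It claims none; its fault is a reason that its next sentence contradicts.
- *That dose choice for Phase III rests on these tests.* No section says so. The stated aim is to identify safe doses, and the secondary objective is to review candidate endpoints.

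It also stands that there is no primary efficacy endpoint, that the sample size rests on feasibility, and that mean estimates with 95% confidence intervals are planned for EVLWI. Strong control is not obligatory in such a trial. But the protocol chose to claim it, and the claim should be true of the rule it states.

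**Conclusion.** The point holds as a mismatch between a stated property and a written rule. As written, the EVLWI procedure controls the error when no dose works, but not in the strong sense. The familywise error is at most 9.4%, and 7.9% at the planned 125 mg effect with both lower doses null, against at most 5.0% for a strict sequence.

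The figures assume that all three doses are completed, 20 patients per dose are compared with 35 pooled placebo patients, all are analysed, variances are equal, and each comparison is at two-sided 0.05. Baseline adjustment was not modelled.

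Because the analyses are secondary and preliminary, the consequence is confined to which lower doses may be reported as significant for EVLWI. It does not affect the safety objective or the comparison of 125 mg with placebo.

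**What to change.** In the EVLWI section, replace the gating sentence with a strict fixed sequence over the completed doses, from highest to lowest. Each dose is compared with placebo at two-sided 0.05 only if the preceding higher dose was significant. After the first non-significant step, give estimates and 95% confidence intervals only. Wording it over completed doses also covers an escalation that stops early.

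In the VFD section, delete the rationale that only the highest dose is compared. Then either adopt the same sequence or label the lower-dose comparisons as unadjusted.

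Section 20a needs no change.

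The cost is about two sentences of text and one loss: 5 mg cannot be declared significant if 60 mg fails. If the sponsor does not want that dependence, keeping the present gate and testing each lower dose at 0.025 also holds the error at no more than 5.0%, at the price of a stricter level for each lower dose.
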